### Eligibility criteria

The sample of the study will be identified according to the following inclusion criteria: a) caregivers are legal guardians of children who receive GHt in accordance with approved indications in Spain, and b) adherence to GHt monitored in the last month prior to enrollment indicates a ratio less than 85%, since it has been considered as an index of relatively sub-optimal adherence [40, 41]. Also, participation in the study requires: c) explicit agreement on data sharing regarding adherence to GHt gathered through the Easypod Connect, d) participants must be able to interact and willing to install, the DH solution of the study in their smartphone, and e) participants must sign the specific ICF for the study.

Consequently, exclusion criteria define those candidates without an Android smartphone or not being able to interact with it cannot participate in the study, because the solution only works through this operative system. Moreover, only one legal guardian per child can participate in the study, and participants in SS1 will not take part in SS2.

### Recruitment

Participants will be recruited from the Pediatric Endocrinology unit at the Miguel Servet Children’s University Hospital. This public hospital provides pediatric health attention to the regional area of Zaragoza (Spain), which covers an approximate 367,110 inhabitants. Participants will be recruited at the pediatric unit by the study site investigator, which is a pediatric endocrinologist experienced in the management of children with growth disorders and their associated team. Enrollment in the study will be based on the information available in the Electronic Health Record (EHR) of potential participants. Whenever a candidate is found suitable, participation in the study will be offered during routine consultations. Participants will sign an informed consent during routine clinical visits to the center. For accessing treatment, adherence data (via Easypod-Connect) of children aged 12 years old and over, a specific ICF will need to be signed according to the Spanish regulation.

Participants will be free to discontinue the study at any time. Reasons to abandon the study will be recorded in the Electronic Case Report Form (eCRF; e.g., no perceived benefit of the mHealth solution, failure to attend the scheduled visit, etc.).

### Planned study DH intervention

SS1 will consists of three visits:Enrolment: participants will sign the ICF and complete a paper-based questionnaire on demographic variables. The estimated recruitment duration has been established in a time of 3 months.Baseline assessment: participants will complete a paper-based questionnaire on anxiety, depression and stress (for more details, see the 2.5 section on the outcome variables). After answering to the questionnaire, participants will download on their own smartphone the DH solution Adhera Caring and a training on how to use this tool will be provided. Participants will take Adhera Caring with them to home and could use it as often as they like.Post-assessment (follow-up visit): after one month, during the standard care visit, participant will participate in a semi-structured interview.

SS2 will include the same visits of the SS1 and the estimated recruitment duration has been established in a time of 6 months. Psychological distress, positive affect, self-efficacy, mental wellbeing, and children’s quality of life will be collected at baseline and follow-up visits using paper-based questionnaires. In addition, a system usability questionnaire will also be administrated during the last visit (Fig. 5).

**Fig. 5 Fig5:**
[figure not shown]
Standard Protocol Items: Recommendations for Interventional Trials (SPIRIT). Schedule of enrollment, interventions, and assessments planned in the study

### Outcome variables

#### Research question 1 (Primary outcome)

Initially, the study aims to understand the psychological burdens experienced by caregivers of children undergoing GHt, and the perceived barriers/facilitators concerning the adoption of a DH solution. To do so, a group of ten caregivers will engage with the DH solution for 1 month. Subsequently, an ad hoc semi-structured interview based on mental health and technology acceptance theoretical framework [42] will serve to gather qualitative information about those user experiences (SS1; see Additional File 2). Such qualitative information will be contextualized by minimal quantitative data in terms of demographics (caregiver: age, gender, marital status, employment status, education level according to the European Qualification Framework [43]; children (patient): age, gender) screening of caregivers’ current level of psychological distress and usability and engagement with the solution. The following instruments to assess these outcomes:*Psychological Distress*: DASS-21 (Depression, Anxiety, Stress Scale; [44, 45]; Cronbach’s alpha 0.90—0.96). The scale contains 21 items with three subscales assessing symptoms of depression (e.g., I felt I wasn’t worth much as a person), anxiety (e.g., I felt scared without any good reason), and stress (e.g., I found it difficult to relax) during the last week. Scores range from 0 (never experienced) to 3 (almost always). Total scores represent general psychological distress.*System Usability*: SUS (System Usability Scale; [46]; Cronbach’s alpha 0.92). 10-item scale based on a 5-point Likert scale measuring strength and agreement of usability (e.g., I thought the solution was easy to use).*Engagement:* Measured by means of user logs including mobile-based user profiling.

#### Research question 2 (Primary and Secondary outcomes)

SS2 will assess, as a primary outcome, caregivers’ positive affect related to the use of the DH solution. In this case, caregivers will engage with the solution for three months.*Positive Affect*: the positive affect subscale of the PANAS (Positive and Negative Affect Schedule (PANAS; [47]; Cronbach’s alpha 0.92) will be used. This subscale is composed of 10 items and will evaluate experienced positive states (e.g., enthusiastic) from 1 (“never”) to 5 (“very much”) during the last month.

SS2 will also explore whether using the DH solution affect psychological distress by the DASS-21 and:*Mental Wellbeing*: the MHC-SF (Mental Health Continuum in Short Form; [48, 49]; Cronbach’s alpha 0.94) evaluates from 0 (“never”) to 5 (“Every day”) the felt experience during the last month regarding three dimensions of mental wellbeing: emotional (e.g., I felt happy), psychological (e.g., I liked most parts of my personality), and social wellbeing (e.g., I belonged to a community).*Self-Efficacy*: the GSE (General Self-Efficacy Scale; [50, 51]; Cronbach’s alpha 0.90) is a 10-item scale assessing perceived self-efficacy (e.g., “I can solve most problems if I invest the necessary effort”) from 1 (“not at all true”) to 4 (“exactly true”).

### Research question 3

Finally, SS2 will also explore several dimensions related to the children’s quality of life and GHt adherence.The parents' version of the *QoLISSY* (Quality of Life Inventory Short Stature Youth; [52]; Cronbach’s alpha 0.78—0.96) will be used to assess QoL dimensions. It includes three core sub-scales, physical (6 items; e.g., Because of my child's height (s)he has more trouble reaching things than others his/her age), social (8 items; e.g., Because of his/her height (s)he is treated differently), and emotional (8 items; e.g., Because of his/her height (s)he is shy) aspects of HrQoL. Additional sub-scales cover coping (10 items; e.g., When (s)he feels bad about his/her height (s)he tries to think of something nice), beliefs about height (4 items; e.g., My child believes that being tall helps in life), and specific questions for parents (11 items). These items refer to parents’ worries about the future of their child in relation to his short stature and effects of the child’s short stature on the parents’ feelings (e.g., My child worries about whether (s)he will grow enough). The items are responded from 0 (“not at all”) to 4 (“always”).*Children’s Quality of Life*: the parent version of the KIDSCREEN-10 ([53]; Cronbach’s alpha 0.82) contains 10 items (e.g., has your child felt well and fit?) in 5 point Likert response format, from “not at all” to “extremely”.

Finally, behavioral parameters in terms of usability (by the SUS) engagement (by logs) with the DH solution will be measured together with children’s adherence to the treatment through the Easypod Connect (time, date and dose) [35]

### Data management and quality control

All the data gathered in the study will be recorded in an electronic case report form (eCRF). This eCRF will be built upon the OpenClinica suite Community v3.4. The main purpose of the eCRF is to obtain data required by the study in a complete, accurate, legible, and timely manner. The data in the eCRF will be consistent with the relevant source documents.

The clinical investigator is responsible for ensuring that the data collected in the course of this study is accurate and documented appropriately on all applicable forms. Data will be processed, evaluated, and stored in anonymous form in accordance with the data protection regulation. The clinical investigator must ensure that the eCRFs and any other associated documents contain no mention of any subject names. The data will be entered into a validated database. Database lock will occur once quality control and quality assurance procedures and coding activities have been completed.

### Data analysis plan

Qualitative data in SS1 will be gathered by means of video/audio interview recordings, which need to be transcribed and coded, first, to be able to manage a more standard dataset. Subsequently, all recordings will be deleted to preserve participants’ anonymity. At least two different reviewers conduct data analyses, independently. Through the iterative process, themes and subthemes will be identified and coded as barriers or facilitators associated with the use of the eHealth solution (Deductive part). Thematic content analysis will be performed afterwards (Inductive part) (37, 54). Descriptions of demographic, clinical, and usability data will be reported in a specific section.

Quantitative data in SS2 will be gathered in a different dataset. Descriptions of demographic and the study outcomes (frequencies, mean, standard deviation, median, maximum-minimum values data, skewness, and kurtosis) will be reported in a specific section. To analyze intervention effects on the primary outcome (i.e., Positive Affect), one sample t-test between baseline and 3-month follow-up scores will be performed. Similarly, pre-post data regarding the secondary outcomes (I.e., psychological distress, self-efficacy, mental wellbeing, and children’s quality of life) will also be examined by t-tests. Bonferroni correction will be used to account for multiple comparison testing. A non-parametric approach (I.e. Mann- Whitney *U* test) will be used in the case that the data shows departures from normality distributions.

In addition, exploratory analyses will also include correlations to identify relevant associations between demographic, primary, secondary outcomes, as well as, childrens’ QoL, treatment adherence, and usability.

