### Sample size

In qualitative research, the sample size cannot be conclusively estimated since it is determined by the saturation of the data acquired during the analysis of the qualitative data (e.g., semi-structured interviews). However, the sample size in SS1 has been estimated as n = 10, based on similar studies assessing the acceptance of a mobile solution, wherein the sample size for interviews and feasibility pilots was between 10–20 participants [36, 37]. Data saturation in the qualitative thematic analysis is expected to be achieved in less than ten subjects due to the focused nature of the study. In the case that this saturation is not achieved, the sample will be extended to include ten more participants.

In SS2, a sample size of n = 55, has been estimated by the GPower v.3.1.9.2 software. Specifically, a study design with 55 participants is appropriate to detect a low-to-medium effect size (Cohen’s *d* = 0.40) with a probability of α = 0.05 associated with a power of 1—ß = 0.08. The estimation is based on mean group differences between the baseline assessment and 3-months of follow-up (i.e., two-sided one-sample t-test).

Participants will be followed after Informed Consent Form (ICF) signature at the hospital to the end of the data collection period. It should be noted that in SS1, participants would engage with the solution for 1 month after recruitment. Since SS1 mainly focuses on usability, we estimated a period of one month, so that participants have a reasonable time to test the DH solution and subsequently rise concerns, barriers or facilitators when using the app. During this one-month observation time, participants will be supported if any doubt or concern arises.

In SS2 participants will be able to engage with the solution, for 3 months. The timing has been established on the standard mindfulness-based training programs that last a minimum of eight weeks [38]. Since the DH solution is self-administered, we added one extra month so that participants have more time to engage with the proposed activities. Major protocol amendments, if any, will be rigorously handled and updated at the ClinicalTrials.gov registry. The present study protocol has been elaborated following the recommendations for study protocols [39] based on the CONSORT extension statement for feasibility trials and the Standard Protocol Items: Recommendation for Interventional Trials (SPIRIT; see Additional file 1).

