## Results

The recruitment process for the SS1 is planned to start by June 2021 and the qualitative analysis is expected to be done by September 2021. Regarding SS2, the recruitment process is planned to start by January 2022 and the primary impact analysis is foreseen to be conducted by February 2023. This protocol describes a novel approach to the mental wellbeing of caregiver of children undergoing a stressful treatment such as the GHt. Furthermore, the protocol presents a scalable tool showing how a collaboration between companies and public health care system might promote such technology into the global health care market.

According to our research questions and hypothesis, we will expect that:In SS1, the usability of the designed DH solution will be acceptable. Furthermore, in SS2 we expect high scores in the SUS (Hypothesis 1).A decrease on the levels of psychological depression, anxiety, and measured by the DASS-21 (Hypothesis 2)An improvement of positive affect (by the PANAS), self-efficacy (by the GSE), and mental wellbeing (by the MHC-SF), and particularly, emotional and psychological wellbeing. (Hypothesis 2)Finally, those psychological variables are positively associated with the children’s quality of life and treatment adherence. (Hypothesis 3).

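### Sub-study 2 is sized at an uncorrected alpha of 0.05, but the stated Bonferroni correction does not exempt the primary test; if that test is included, power falls from 83% to about 62% or less

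*Protocol article*

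**What the plan says.** **Sizing.** In the Protocol article, section Sample size: "In SS2, a sample size of n = 55, has been estimated by the GPower v.3.1.9.2 software". That number is said to be "appropriate to detect a low-to-medium effect size (Cohen’s *d* = 0.40") "with a probability of α = 0.05 associated with a power of 1—ß = 0.08". The test is given as "i.e., two-sided one-sample t-test" on the change from baseline to 3 months. The section mentions no adjustment for multiple testing.

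**Primary outcome.** Research question 2 names one: "SS2 will assess, as a primary outcome, caregivers’ positive affect related to the use of the DH solution".

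**Analysis.** The Data analysis plan gives the primary test first: "one sample t-test between baseline and 3-month follow-up scores will be performed". It then applies t-tests in the same way to four secondary constructs: psychological distress, self-efficacy, mental wellbeing and children's quality of life. The next sentence is "Bonferroni correction will be used to account for multiple comparison testing". It does not say which tests form the family, does not count them, and neither includes nor exempts the primary test by name.

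**The concern.** The sample size and the analysis can be read as using different significance levels for the same test. The Sample size section names no outcome, but its pre-post one-sample t-test is the one planned for positive affect, and it uses the whole 0.05. The Bonferroni sentence closes a list holding both the primary and the secondary tests, so on its plain reading it covers them all. The primary test would then be run at 0.05 divided by the number of tests.

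Two things are at stake. First, power: a study sized at 0.05 and analysed at 0.01 no longer has the power its sample size was meant to give. Second, the decision rule: two analysts following the same text could judge the same primary result differently.

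**Working it through.** **Inputs**
- n = 55, d = 0.40, two-sided alpha 0.05, one-sample t-test on the pre-post difference (Sample size).
- Power is printed as 0.08. Assumption: 0.80 was meant, since 55 participants at d = 0.40 give far more than 8%.
- Assumption: all 55 are evaluable. The article gives no dropout rate.
- Number of tests, m: one primary plus four secondary constructs gives m = 5 (Data analysis plan). Research question 3 describes two child quality-of-life instruments, QoLISSY and KIDSCREEN-10; counting both gives m = 6.

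**Formula.** Degrees of freedom are n − 1 = 54. The noncentrality parameter is d × √n = 0.40 × √55 = 2.966. Power is the probability that a noncentral t variable with these parameters lies beyond ±t(1 − alpha/2m; 54).

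**The plan's own figure.** At alpha 0.05 the critical t is 2.005 and power is 83.0%. Exactly 80% power would need 52 participants, so 55 is slightly generous for the stated inputs. A 5% allowance for dropout would explain it (52/0.95 = 54.7, rounded up to 55), but none is stated.

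**Primary test inside a Bonferroni family**

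| Tests in family | Alpha per test | Critical t | Power at n = 55 | n for 80% power |
|---|---|---|---|---|
| 1 (primary exempt) | 0.05 | 2.005 | 83.0% | 52 |
| 5 | 0.05/5 = 0.0100 | 2.670 | 61.8% | 77 |
| 6 | 0.05/6 = 0.0083 | 2.739 | 59.2% | 80 |

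The loss is 83.0 − 61.8 = 21.2 percentage points with five tests and 83.0 − 59.2 = 23.8 with six.

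**Detectable effect at n = 55 and 80% power.** d = 0.38 with the primary exempt and about 0.48 with five or six tests (0.476 and 0.485).

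**Sensitivity to family size.** Larger families lower power further: about 50% at 12 tests and 47% at 15. Those counts need separate tests of DASS-21, MHC-SF and QoLISSY subscales, which the analysis section does not announce, so they are outer scenarios only.

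**Sensitivity to loss.** With an assumed loss of about 10% (49 evaluable), power is 78% with the primary exempt, 55% with five tests and 52% with six.

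**The case against.** The strongest reply is that nothing conflicts. The article names one primary outcome and sizes for it at 0.05. The correction comes directly after the secondary tests and can be read as covering only those. On that reading power is 83%. This stands as a possible reading, so low power cannot be asserted as a fact. It does not settle the matter, because the text does not choose between the readings and the unqualified sentence follows both sets of tests.

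A second reply is that this is a condensed article on a single-group, exploratory feasibility study, and that a full list of tests commonly sits in an analysis plan not shown here. That also stands. The absence of a list is not the point. The point rests on the printed alpha and the printed correction. Including the primary would also be conservative: it costs power and does not inflate false positives.

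Three stronger readings are tempting, and the documents do not support them:
- A reader might infer that the primary test simply has 50–60% power. That requires the primary to be in the family and a family of 6 to 11 tests. The plainest count is five, which gives 62%.
- A reader might infer a divisor of 12 or 15 from the expectations listed under Results, which single out "particularly, emotional and psychological wellbeing". That is a list of expectations, not of tests, and Research question 1 says the DASS-21 total represents general distress.
- A reader might see a contradiction in child quality of life being both explored and tested as secondary. The article uses the same verb for distress, mental wellbeing and self-efficacy, which are plainly secondary.

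**Conclusion.** The point holds as a conditional mismatch. The sizing uses an uncorrected 0.05, and the announced correction, as worded, does not exempt the primary test. If the primary is inside the family, its power at d = 0.40 is about 62% (five constructs) or 59% (six tests), and lower if subscales were also tested. If it is exempt, power is 83%. All three figures take 55 evaluable participants; reading the printed power as 0.80 bears only on what the plan intended.

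A reader might also infer that the significance threshold is free to be chosen after the data are seen. The article does not establish this, since a fixed list may exist elsewhere. What it does establish is that the alpha for the single primary test cannot be read from the text. That should be settled before analysis, because it decides any primary p-value between the corrected threshold and 0.05.

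**What to change.** In the Data analysis plan, state that positive affect is the single primary outcome of sub-study 2 and is tested at two-sided 0.05, outside any correction. This matches the existing sample size.

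Apply the correction only to the four secondary constructs, using Holm in place of Bonferroni: it controls the same familywise error and is never less powerful. Prespecify one total score per construct, which includes naming the instrument that represents children's quality of life. Report subscales as estimates with 95% confidence intervals.

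If the sponsor prefers to keep the primary in the family, the Sample size section should instead give power of about 62% for five tests, or a detectable effect of about d = 0.48 at 80% power. Holding 80% power at d = 0.40 would take 77 evaluable participants for five tests or 80 for six.

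The first option costs about two sentences and no extra participants or data. Its downside is that subscale results carry no formal claim of significance. The printed power of 0.08 should be corrected in the same edit.

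### Plain Bonferroni for the SS2 secondary outcomes is valid, but Holm's step-down gives the same error control and never rejects less; the gain is roughly 0 to 11 points of power per outcome

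*Protocol article*

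**What the plan says.** In the protocol article, the Data analysis plan gives SS2 one primary test: "To analyze intervention effects on the primary outcome (i.e., Positive Affect), one sample t-test between baseline and 3-month follow-up scores will be performed". The secondary outcomes are then handled in the same way: "psychological distress, self-efficacy, mental wellbeing, and children’s quality of life) will also be examined by t-tests". The next sentence fixes the multiplicity method: "Bonferroni correction will be used to account for multiple comparison testing". It does not say how many tests are corrected or whether the primary test is among them.

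The only power statement is under Sample size: "In SS2, a sample size of n = 55, has been estimated by the GPower v.3.1.9.2 software", for a standardised effect of 0.40, "with a probability of α = 0.05 associated with a power of 1—ß = 0.08", using a "two-sided one-sample t-test". No effect size, power target or correlation is given for any secondary outcome.

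Hypothesis 2 (Background, repeated under Results) expects improvement in distress, positive affect, self-efficacy and mental wellbeing. Positive affect is the primary outcome, so three of the four named secondary outcomes are covered. Children's quality of life falls under research question 3, and Hypothesis 3 expects it to be associated with the caregiver measures.

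**The concern.** Bonferroni compares every p-value with 0.05/m, whatever the other tests show. Holm starts at the same threshold but relaxes it after each rejection. Both hold the family-wise error at 0.05 with no assumption about dependence between outcomes. Holm's rejections always include Bonferroni's, so on error control and power there is no reason to prefer the single-step version.

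The difference matters when several effects are real at once, which is what Hypothesis 2 predicts. A true change in distress, self-efficacy or mental wellbeing could then be reported as non-significant under Bonferroni and significant under Holm, from the same data. The Discussion presents the study as work towards a randomised trial, and these secondary signals would inform that step.

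**Working it through.** **Inputs**
- n = 55, d = 0.40, two-sided alpha 0.05, one-sample t-test on change scores (Sample size).
- m = 4 secondary outcomes: distress, self-efficacy, mental wellbeing, children's quality of life (Data analysis plan).
- Assumptions: d = 0.40 for each secondary outcome that truly changes; equal correlation of 0, 0.3, 0.5 or 0.7 between change scores; all 55 participants analysed; the primary outcome outside the family.

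**The plan's own figure.** The power is printed as 0.08 and is read here as 0.80, which is an assumption. Power of the two-sided test is P(|T| > t(1 − α/2, n − 1)), where T is non-central t with n − 1 degrees of freedom and non-centrality d√n. For n = 55 the non-centrality is 0.40 × √55 = 2.97, and power at 0.05 is 83.0%. The exact calculation needs n = 52 for 80% (n = 51 gives 79.99%, n = 52 gives 80.8%). So n = 55 is not reproduced exactly, but it lies slightly on the safe side.

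**Thresholds.** Bonferroni uses 0.05/4 = 0.0125 for all four tests. Holm uses 0.05/4, 0.05/3, 0.05/2 and 0.05/1 in order of the p-values, stopping at the first failure. Power of a single test at each threshold, n = 55, d = 0.40:

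| Threshold | Power |
|---|---|
| 0.0125 | 64.9% |
| 0.0167 | 68.9% |
| 0.025 | 74.4% |
| 0.05 | 83.0% |

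Bonferroni therefore has 64.9% power for each real effect, whatever the others do. Holm lies between 64.9% and 83.0%, depending on how often the other tests are rejected first.

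**Gain of Holm over Bonferroni**, in percentage points per real effect (simulation, 50,000 trials per cell, d = 0.40):

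| Real effects out of 4 | corr. 0 | corr. 0.3 | corr. 0.5 | corr. 0.7 |
|---|---|---|---|---|
| 1 | 0.2 | 0.1 | 0.1 | 0.0 |
| 2 | 2.7 | 2.6 | 2.4 | 2.2 |
| 3 | 6.2 | 5.8 | 5.4 | 5.0 |
| 4 | 11.4 | 10.3 | 9.4 | 8.6 |

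Reading down, the gain grows with the number of real effects. Reading across, it shrinks slightly as correlation rises.

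**Other summaries**
- All four real: the chance that all four are declared is 27.6% with Bonferroni and 52.2% with Holm at correlation 0.3, and 34.6% against 57.5% at 0.5.
- The chance of at least one rejection is identical, because both methods use 0.0125 for the smallest p-value (94.3% for both with four real effects at correlation 0.3).
- The simulated family-wise error of Holm was at most 4.4% in these four-outcome scenarios.

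**Sensitivity to the borrowed effect size.** With all four real and correlation 0.3, the gain is 2.3 points at d = 0.2, 7.1 at d = 0.3 and 7.2 at d = 0.5.

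**Sensitivity to the family.** If the primary outcome were included (m = 5, threshold 0.01), Bonferroni power is 61.8%, and Holm adds 9.6 to 12.6 points if all five effects are real.

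**The case against.** The strongest reply is that nothing here is wrong. Bonferroni is prespecified, conservative, simple and valid under any dependence, and it has matching simultaneous confidence intervals, which Holm does not readily give. The study is described as exploratory, the secondary outcomes are to be explored, and no decision rule in the article rests on their significance. The same remark could be made about almost any plan that uses Bonferroni. All of this stands, and it sets the severity. It does not remove the point, because the article itself names the method and a procedure with the same guarantee and at least as many rejections is available at almost no cost.

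Three stronger readings are tempting, and the document does not support them.
- A reader might infer that SS2 loses about 10 points of power on every secondary outcome. That needs all four to change by 0.40. The article assumes this for none of them, and Hypothesis 2 covers only three.
- A reader might infer that the loss buys nothing. Bonferroni does keep simple simultaneous intervals, although the plan does not request them.
- A reader might infer that correlation between the outcomes makes Bonferroni especially wasteful relative to Holm. Holm does not exploit correlation, and the table shows the gain falling slightly as correlation rises.

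That the family size is not stated is no finding in itself. Such detail is commonly left to the full protocol or analysis plan, which is not shown.

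**Conclusion.** The point holds as a low-severity efficiency improvement. If the three secondary outcomes named in Hypothesis 2 truly change by 0.40 and children's quality of life does not, Holm raises power per real effect from about 65% to about 70 or 71%. The full range across the four-outcome scenarios at d = 0.40 is about 0 to 11 points, governed mainly by how many effects are real. The figures rest on an effect size borrowed from the SS2 sample-size calculation, a family of four and no missing data. That Holm never rejects less rests on none of these. If the family holds only the secondary outcomes, the primary test and the basis for n = 55 are unaffected.

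**What to change.** Replace the Bonferroni sentence in the Data analysis plan by: *The secondary outcomes form one family; the Holm step-down procedure controls the family-wise error at two-sided 0.05.* Report each mean change with an ordinary 95% confidence interval beside the Holm-adjusted p-value, and label the intervals as unadjusted, since an interval may exclude zero while the adjusted p-value exceeds 0.05.

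This wording leaves the primary outcome to be tested alone at 0.05. If the sponsor intends it to be inside the family, the sentence should say so.

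The cost is one sentence, with no extra data or visits. The change should be made before any SS2 outcome data are examined. The one downside is the absence of simple matching simultaneous intervals. If the sponsor wants those, keeping Bonferroni is defensible.

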## Methods

### Design and setting

This is a prospective mixed-methods usability and feasibility study intervention, see Additional File 1 for SPIRIT diagram. The study will be composed of two single group sub-studies (SS1 and SS2) targeting caregivers of children undergoing GHt in accordance with general clinical practice in Spain and the Miguel Servet Children’s University Hospital (Zaragoza, Spain) where patients are already supervised by a pediatric endocrinologist.

The goal of sub-study 1 (SS1; n = 10) is to gain qualitative insights about psychological burdens experienced by caregivers of children undergoing GHt, and barriers/facilitators after using the DH solution for one month. Insights from SS1 will serve to provide an optimized version of the mobile solution for its use in sub-study 2 (SS2; n = 55). In this case, psychological parameters in terms of psychological distress, positive affect, mental wellbeing, and self-efficacy will be targeted and assessed before and after using the DH solution (pre-post design). Children’s quality of life, treatment adherence, and system usability.

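### The non-parametric fallback for SS2 is an independent-samples test (Mann-Whitney U) although the data are paired; power is then lost to a degree set by the unstated pre-post correlation

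*Protocol article*

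**What the plan says.** Under Design and setting, the protocol article describes "two single group sub-studies (SS1 and SS2"), with the SS2 psychological measures "assessed before and after using the DH solution (pre-post design"). There is no comparator arm.

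Under Sample size, SS2 has "a sample size of n = 55, has been estimated by the GPower v.3.1.9.2 software", said to be "appropriate to detect a low-to-medium effect size (Cohen’s *d* = 0.40") "with a probability of α = 0.05 associated with a power of 1—ß = 0.08". The basis is given as: "The estimation is based on mean group differences between the baseline assessment and 3-months of follow-up (i.e., two-sided one-sample t-test").

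Under Data analysis plan, positive affect is tested with the same one-sample t-test between baseline and 3 months. Distress, self-efficacy, mental wellbeing and the children's quality of life are also tested with t-tests, with a Bonferroni correction. The fallback follows: "A non-parametric approach (I.e. Mann- Whitney *U* test) will be used in the case that the data shows departures from normality distributions". No section names a paired rank test, and the plan contains no between-group comparison to which an independent-samples test could apply.

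**The concern.** A one-sample t-test between two time points makes sense only on each caregiver's own difference. The Mann-Whitney U test does not use those differences. It would rank 55 baseline and 55 follow-up scores together as if they came from 110 unrelated people. Its null variance assumes independence, which two measurements on the same caregiver will not normally satisfy. When the two scores are positively correlated, that variance is too large, so the test rejects too rarely both under the null and under a real change.

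The trigger is also loosely worded. It refers to the normality of the data, without saying whether that means the raw scores or the differences. The t-test's assumption concerns the differences. As written, skew in the raw scores alone could cause the switch.

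At stake is whether n = 55 still supports detection of the planned change once an outcome goes to the fallback. The Discussion places the study on the way to a randomised trial, so a falsely null result could mislead that step.

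**Working it through.** **Inputs from the article.** n = 55; standardised change 0.40; two-sided α = 0.05; one-sample t-test (Sample size). The printed power of 0.08 is read here as 0.80; that misprint is a separate matter. **Assumed, because not stated:** the pre-post correlation ρ (range shown), bivariate normal scores with equal variances, no dropout, no Bonferroni adjustment.

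**1. The plan's own figure.** Normal approximation: n = ((1.960 + 0.842)/0.40)² ≈ 49.1, so 50. The exact noncentral-t calculation needs n = 52 for power 0.80 (n = 51 gives 0.7999). At n = 55 the noncentrality is 0.40 × √55 = 2.97 and power is 0.830. The stated 55 is therefore not reproduced exactly, but it is slightly generous for the named test. The design does rest on a paired analysis.

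**2. The matching rank test.** For normal differences the signed-rank test has asymptotic relative efficiency 3/π. The effective n is 55 × 3/π = 52.5, giving power 0.812. Simulation (20,000 runs per ρ) gives about 0.81 at every ρ, with type I error about 0.05.

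**3. The named test on the paired data.** If 0.40 is in SDs of the differences, as the one-sample t-test implies, the shift in raw-score SDs is 0.40 × √(2(1 − ρ)). The Mann-Whitney statistic then has approximate mean [0.40 × √(2(1 − ρ)) / √(2/55)] × √(3/π) and SD √(1 − ρ), while the test uses SD 1. At ρ = 0.5 the mean is 0.40/0.1907 × 0.977 = 2.05 and the SD is 0.707. Power is approximately Φ((2.05 − 1.96)/0.707) = 0.55. Simulation (20,000 runs per ρ) gives:

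| ρ | Mann-Whitney power | Type I error | Share of 0.83 lost |
|---|---|---|---|
| 0 | 0.82 | 0.051 | (0.83 − 0.82)/0.83 = 1% |
| 0.3 | 0.70 | 0.020 | 16% |
| 0.5 | 0.54 | 0.008 | 35% |
| 0.6 | 0.42 | 0.003 | 49% |
| 0.7 | 0.26 | 0.001 | 69% |
| 0.8 | 0.09 | 0.0001 | 89% |

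**4. The other reading of 0.40.** If 0.40 is in raw-score SDs, the Mann-Whitney mean is 2.05 whatever ρ is, and power is approximately Φ(0.09/√(1 − ρ)), just over one half. Simulated values are about 0.53 to 0.57 for ρ from 0 to 0.8. The paired standardised change is 0.40/√(2(1 − ρ)): 0.283 at ρ = 0, 0.40 at 0.5 and 0.516 at 0.7. Signed-rank power is then 0.52 to 0.55 across runs at ρ = 0, 0.81 to 0.82 at 0.5, and 0.96 at 0.7. The named test gains almost nothing from the pairing, while the paired test gains a great deal.

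**The case against.** A reader might infer that most of the planned power is lost whenever the fallback is used. The article does not support that. It gives no correlation, and the loss ranges from almost nothing at ρ = 0 to nearly all at 0.8, passing one half only above about 0.6. The steep fall also depends on holding the change at 0.40 SD of the differences, so that the raw shift shrinks as ρ rises. On the raw-score reading, Mann-Whitney power stays above one half throughout.

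Other limits also stand:

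- The simulated data are normal, so they would not themselves trigger the fallback. They isolate the effect of ignoring pairing and do not predict power under real non-normality.
- The t-test is the default for every outcome. Only outcomes judged non-normal are affected, so it would be wrong to say that the primary and all secondary results are compromised.
- With positive correlation the error is conservative. It does not produce false claims of benefit, and the study is exploratory.
- The data in the trigger may already mean the differences, and details of the normality check may sit in an analysis plan that is not shown.
- The test name may be a slip for the signed-rank test.

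None of this rescues the sentence. A condensed article may leave detail out, but here it names a specific test that does not fit its own design. An analyst following the text would run that test. Correcting it after seeing the data would be a post hoc change, possibly to the primary analysis.

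**Conclusion.** The fallback is wrong as written: an independent-samples rank test is assigned to a single-group pre-post comparison. For any outcome that goes to it, positive correlation makes the test conservative and costs power. Under normality, n = 55 and a change of 0.40 SD of the differences, about a third of the planned power is lost at ρ = 0.5, about half at 0.6 and about two thirds at 0.7. A paired rank test would keep about 0.81. These sizes are conditional on a correlation that the article does not state and on an unadjusted 5% level. The mismatch between test and design depends on neither.

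**What to change.** In the Data analysis plan, replace the Mann-Whitney U test with the Wilcoxon signed-rank test on within-caregiver differences (3 months minus baseline), and state that normality is judged on those differences. The edit is best made before any SS2 outcome data are examined. It costs one sentence and changes neither the sample size, the visits nor the data collected.

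Reporting a Hodges-Lehmann median change with its interval, or keeping the t-test as primary with the signed-rank test as a sensitivity analysis, would be reasonable choices. They are preferences and are not needed to correct the error.
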